### Assessment

Assessments will be conducted at baseline and 4, 12 and 24 months by staff blinded to participant allocation. Each assessment time point will comprise two facility-based visits approximately one week apart, the first for 90 min, and the second for 60 min. At visit 1 (90 min) participants will provide a blood sample and complete physical activity and health-related quality of life questionnaires. The Short Physical Performance Battery (SPPB) and 6-min walk test (6MWT) will be undertaken. An assessment of ABPI will be performed. Smoking status, medical and surgical history, anthropometry, resting heart rate, brachial blood pressure and ambulatory ability will also be assessed. At the end of visit 1, participants will be fitted with an activPAL3™ accelerometer, which will be worn for seven consecutive days. At visit 2 (60 min), participants will return the activPAL3™ accelerometer, and complete additional physical activity and health related quality of life questionnaires. At baseline only, the six minute walk test is repeated at visit 2. Participants will be given the written PAD information sheet at the end of visit 2. Assessments at 4, 12 and 24 months will also include the recording of any study defined clinical events since the previous visit.

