Between group differences in physical activity (primary outcome) and other measures will be analysed using an intention-to-treat approach and repeated measures mixed models. All continuous data will be inspected for normality of distribution visually and statistically, and non-normally distributed data will be mathematically transformed if possible prior to use with parametric statistics. Covariates considered for use in these models include age, gender and any characteristics significantly different between groups at baseline which could potentially confound the variable of interest in each model. Predictors of changes in primary and secondary outcomes will be identified using simple and multiple regression models of relevant baseline characteristics (e.g., BMI and education). The incidence of revascularisation in the intervention and usual care control groups will be compared by chi-square test or logistic regression adjusted for relevant baseline characteristics if needed. Binomial logistic regression will be conducted to identify factors that predict revascularisation. Differences in time to revascularisation will be analysed by Kaplan Meier analysis and log rank test. Given the low risk of the behavior intervention planned in this study it is highly unlikely that the trial would require stopping and thus no interim analysis is planned. Relative effect sizes and 95 % Confidence Intervals for primary and secondary outcomes will be calculated. A *p* value of <0.05 will be accepted as statistically significant, given that all hypotheses to be tested have been formulated *a priori.*

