The base case economic evaluation will adopt the perspective of the health sector, meaning that the data analysis will be restricted to including the costs and outcomes that directly impact upon the health sector. Two forms of analysis will be undertaken: a cost-effectiveness analysis and a cost-utility analysis. The cost-effectiveness analyses will compare the direct costs of the intervention (minus any cost savings) against the activity outcomes. An incremental cost effectiveness ratio (ICER) will be calculated as follows:$$ \mathrm{ICER}=\left(\mathrm{C}1-\mathrm{C}0\right)/\left(\mathrm{E}1-\mathrm{E}0\right) $$where C1 is the cost of the intervention (minus cost savings); C0 is the cost of the usual care; E1 is the effect from the intervention; and E0 is the effect of the usual care. C0 includes the costs associated with four separate patient appointments, which comprises of a general conversation, and on-going medical care. The difference between C1 and C0 is the incremental or additional cost being introduced to the health system. Similarly, the difference between E1 and E0 is the incremental effectiveness of the intervention. Within a sensitivity analysis, any working time lost will be converted into productivity costs, thus widening the perspective of the analysis to include some societal costs.

From the information above, three cost-effectiveness ICERs will be generated, as described below. For each ICER, the incremental cost of the intervention will be identical; whereas for effects, three activity outputs will be used. This analysis will then generate: (i) cost per additional 1000 steps/day walked; (ii) cost per additional 100 calories/day expended; and (iii) cost per additional minutes of moderate to vigorous intensity physical activity/day). This analysis will be performed at the 4-month post intervention and 12 and 24 month follow-ups.

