The cost-utility analyses will be then be undertaken. The same direct costs will be included as before, however, in this case, the outcome measure will be changed to quality-adjusted life years (QALYs). Health utility scores will be generated for each participant by converting responses to HRQoL questionnaires into a single score using validated algorithms. The algorithm weights responses to HRQoL questions using population preferences and hence health utility score are also known as (preference-weighted) HRQoL. To estimate a quality-adjusted life year for cost-utility analysis, we will convert the EQ-5D and SF-36 into utility scores (the latter through the SF-6D) [88], and apply Australian utility weights for each [89, 90]. This permits cross-validation checks for the health utility values elicited and exploration of the sensitivity of the incremental outcome to choice of quality of life measure post-intervention. These analyses will be performed at the 12 month and 24 month follow-up. In Australia, a new intervention is generally considered to be cost-effective if the ICER, the mean cost per unitary change in mean utility is ≤ $50,000 [91, 92].

If the intervention is found to successfully improve health outcomes, and to result in reduced time lost from work, then the ‘perspective’ of the analysis would widen from the health sector to incorporate productivity savings. For those of working age, time lost from employment will be estimated using the World Health Organization’s Health and Performance Questionnaire (HPQ) [93]. Working time lost will be converted to productivity losses by using average Gross Domestic Product (GDP) per capita, adjusted pro rata. If individuals are made unemployed (rather than temporary sickness absence) then an assumption will be made regarding the length of time before that position is replaced by another person in the general population. A 90 fractional day period will be assumed, before replacement takes place. Any productivity losses would then be factored into the value of C1 above (reducing it), and the ICERs would be recalculated. This stage of the analysis would be reported separately as these potential productivity savings do not fall under the health care budget, and so is outside of the health sector funder’s perspective.

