Uncertainty analysis will be conducted by bootstrapping patient level data and a value of information analysis (VOI) will estimate the need to undertake further research to inform whether the intervention is value for money [94]. All economic evaluation work will be implemented using STATA and Microsoft Excel® (Microsoft Corporation, Redmond, WA, USA).

Results will be disseminated via relevant scientific (e.g., journals, conferences), professional (e.g., newsletters), and public (e.g., media) forums. There are no plans to use professional writers.

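### The cost-utility analysis names no adjustment of incremental QALYs for the baseline utility it collects; adding one is a free gain in precision

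*Protocol article*

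**What the plan says.** All of the economic text is in the protocol article under Data management and analyses.

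- The ratio is (C1-C0)/(E1-E0), where "E1 is the effect from the intervention; and E0 is the effect of the usual care". The text adds that "the difference between E1 and E0 is the incremental effectiveness of the intervention".
- For cost-utility the costs stay the same and "in this case, the outcome measure will be changed to quality-adjusted life years (QALYs". To obtain them, "we will convert the EQ-5D and SF-36 into utility scores (the latter through the SF-6D"), with Australian weights. On timing: "These analyses will be performed at the 12 month and 24 month follow-up".
- On uncertainty: "Uncertainty analysis will be conducted by bootstrapping patient level data", followed by a value-of-information analysis.

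Under Assessment: "Assessments will be conducted at baseline and 4, 12 and 24 months by staff blinded to participant allocation". Quality-of-life questionnaires are part of each of these assessments, and Secondary outcome measures lists EQ-5D-5L and SF-36 among them. Baseline utility is therefore available for every randomised participant who completes them.

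The only covariate rule sits with the repeated-measures mixed models: "Covariates considered for use in these models include age, gender and any characteristics significantly different between groups at baseline". It does not mention utility, QALYs or the ratio. Randomisation is stratified by ABPI, site and gender, not by quality of life.

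**The concern.** Baseline utility enters a QALY twice: it is the first point of each participant's utility curve, and it predicts every later point. If the arms happen to differ at baseline, part of that difference appears as a QALY gain or loss and sits in the denominator of the ratio. With 100 participants per arm, or about 60 if the full 40 % dropout occurs, some imbalance must be expected.

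The covariate rule for the clinical models would not deal with this even if it were borrowed. It lets a baseline variable in only when the arms differ significantly, so an imbalance just short of significance goes uncorrected. In trials where there is no visible imbalance, the precision available from a strong predictor is not used.

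What is at stake is the width of the interval for incremental QALYs, the stability of the ratio, and the value-of-information result, which depends directly on the remaining uncertainty.

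**Working it through.** **The plan's own figures.** The article states no precision, SD or correlation for QALYs, so there is no QALY figure to reproduce. Its one design figure is 62 per group for steps/day. With means 5000 and 3300 and SDs 3400 and 2200, the pooled SD is sqrt((3400² + 2200²)/2) = 2864. Then n = 2 × (2864 × (1.960 + 1.282)/1700)² = 59.6, so 60 per group, or 61 with the t distribution. That is close to 62. The correlation of 0.6 quoted with it is for physical activity; it is borrowed below as an assumption only.

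**Inputs**

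- Visits at 0, 4, 12 and 24 months (Assessment).
- Up to 100 per arm; 60 per arm after 40 % dropout (Sample size calculation).
- Assumed: QALYs are trapezoid areas under the utility curve, utility variance is equal at all visits, and the correlation ρ is equal between visits.
- ρ = 0.6 as the working value, range 0.3 to 0.8.
- Results are in units of the utility SD. Where a QALY figure is shown, SD = 0.20 is assumed (range 0.15 to 0.25).

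**Weights in years**

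- 24 months: 1/6, 1/2, 5/6, 1/2; sum 2, sum of squares 1.222.
- 12 months: 1/6, 1/2, 1/3; sum 1, sum of squares 0.389.

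**Share of variance removed by adjustment**

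Var(QALY) = ρ × sum² + (1-ρ) × sum of squares. Cov(baseline, QALY) = ρ × sum + (1-ρ)/6. Share removed = Cov²/Var.

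- 24 months, ρ = 0.6: Var = 2.4 + 0.489 = 2.889; Cov = 1.2 + 0.067 = 1.267; share = 1.604/2.889 = 0.555. SE ratio = sqrt(0.445) = 0.67.
- 12 months, ρ = 0.6: Var = 0.6 + 0.156 = 0.756; Cov = 0.667; share = 0.444/0.756 = 0.588. SE ratio = 0.64.

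A simulation of 4,000 trials with 100 per arm gave a 24-month variance ratio of 0.46, against 0.445 from the formula.

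| ρ (equal between visits) | Variance cut, 12 months | Variance cut, 24 months |
|---|---|---|
| 0.3 | 30 % | 25 % |
| 0.4 | 40 % | 35 % |
| 0.5 | 49 % | 45 % |
| 0.6 | 59 % | 56 % |
| 0.8 | 79 % | 78 % |

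If the correlation instead decays with time (0.3 to 0.8 at a 12-month gap), the cut is 53 % to 88 % at 12 months and 30 % to 76 % at 24 months.

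**Size of chance imbalance, 24 months, ρ = 0.6**

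One standard error of the baseline difference is sqrt(2/100) = 0.141 SD with 100 per arm and sqrt(2/60) = 0.183 SD with 60. The expected shift in the plain QALY difference is 1.267 times this.

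- 100 per arm: 0.179 SD-years. At SD 0.20 this is 0.036 QALY (0.027 to 0.045 for SD 0.15 to 0.25).
- 60 per arm: 0.231 SD-years. At SD 0.20 this is 0.046 QALY (0.035 to 0.058).
- An imbalance just under 1.96 standard errors, which the clinical covariate rule would leave alone, shifts the difference by about 0.070 QALY with 100 per arm at SD 0.20.

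The unadjusted SE with 100 per arm at SD 0.20 is 0.20 × sqrt(2.889 × 2/100) = 0.048 QALY, and the adjusted SE is 0.032.

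**If the effect is read as change from baseline**

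Subtracting baseline utility times follow-up time gives, at ρ = 0.6:

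- 24 months: 2.889 + 4 - 4 × 1.267 = 1.822, against 2.889 - 1.604 = 1.284 with regression, so 42 % more variance.
- 12 months: 0.756 + 1 - 2 × 0.667 = 0.422, against 0.756 - 0.444 = 0.311, so 36 % more.

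**The case against.** The strongest reply is that the article never says the QALY comparison is unadjusted. E1-E0 is the generic definition of incremental effectiveness and is compatible with a regression estimate. A fuller protocol or health economic plan, not shown, may specify one. This stands: the text names no adjustment, and that is all that can be said. It does not rule adjustment out. Against it, the economic section is specific about the formula, instruments, weights, threshold, bootstrap and software. The clinical paragraph mentions covariates where adjustment is contemplated, so a reader following the text would compute the plain difference.

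A second reply is that the mixed models cover other measures too, and that the threshold sentence speaks of a change in mean utility, so baseline may already be used. The models are not linked to the ratio. A change score does help, cutting the 24-month variance by 37 % under the assumptions above, but it still leaves more variance than regression.

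Third, no error is hidden. Randomisation keeps the plain difference unbiased, and the bootstrap includes the variation due to baseline imbalance. A one-SE imbalance shifts the estimate by about three quarters of its own unadjusted SE (0.036/0.048), which is ordinary sampling error. This stands in full.

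Two stronger readings are tempting. A reader might infer that about half the precision is lost as a matter of fact. The documents give no utility correlation or SD and no QALY integration rule, so that figure is conditional, and it concerns variance, not interval width. A reader might also infer that imbalance would carry the result across $50,000 per QALY. The documents give no cost difference, so this cannot be shown.

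**Conclusion.** This is a free improvement. It is neither an error in the plan nor a source of systematic bias. As written, the cost-utility analysis leads to an incremental QALY that carries chance baseline imbalance and does not use a strong predictor already collected.

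The size rests on assumptions. With trapezoid QALYs and the between-visit correlation of 0.6 borrowed from steps, the standard error would be about one third smaller. The percentage gain does not depend on the utility SD; the QALY amounts do. The gain is material across every correlation examined, and also against a change-from-baseline analysis at the working correlation, so the recommendation does not depend on the exact value.

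**What to change.** In the economic part of Data management and analyses, or in the health economic plan if one exists, state the following.

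- E1-E0 for QALYs is the arm coefficient from a regression of each participant's 12-month and 24-month QALYs on arm and that participant's baseline utility on the same instrument: EQ-5D for EQ-5D QALYs, SF-6D for SF-6D QALYs.
- The regression is refitted in every bootstrap replicate, with each participant's costs and QALYs resampled together.
- The adjusted estimate is used for the ratio, its comparison with the threshold and the value-of-information analysis.
- The unadjusted difference is reported as a sensitivity analysis.

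Baseline utility should enter whatever its observed imbalance, not through a significance test. If a fuller plan already says this, a cross-reference is enough. The cost is one or two sentences and a regression inside the planned bootstrap; no participants, visits or data are added. The wording should be settled before outcome data are compared by arm.

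### Productivity is planned once as an unconditional sensitivity analysis and once only if results favour the intervention; under the second rule the recalculated ICERs can move only in its favour

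*Protocol article*

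**What the plan says.** Both statements are in the Protocol article, Data management and analyses.

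- **With the ICER formula.** The base case is restricted to the health sector: "The base case economic evaluation will adopt the perspective of the health sector". The cost terms are defined thus: "where C1 is the cost of the intervention (minus cost savings); C0 is the cost of the usual care". Productivity is then added without any condition on results: "Within a sensitivity analysis, any working time lost will be converted into productivity costs".
- **After the cost-utility analysis.** Productivity now depends on the findings: "If the intervention is found to successfully improve health outcomes, and to result in reduced time lost from work". Only then does the perspective widen, to take in productivity savings. Lost time is to be measured by a work-performance questionnaire (HPQ) in those of working age and valued from GDP per capita. The adjustment follows: "Any productivity losses would then be factored into the value of C1 above (reducing it), and the ICERs would be recalculated". This stage is to be reported apart from the health-sector results.

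**The concern.** The two statements cannot both be followed. Suppose participants in the intervention arm lose as much working time as controls, or more. The first statement calls for a productivity result; the second provides none. They differ on direction as well: the first treats lost time as a cost, the second lets productivity act only as a reduction.

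Followed alone, the second statement uses the estimated work-time difference twice, first to decide whether the analysis is done and then as the adjustment itself. Chance differences that favour the intervention are counted as savings, and chance differences against it are left out. Because the trigger also requires better health outcomes, the ICER denominator is positive when the rule applies, so lowering C1 always moves the ratio in the intervention's favour. At stake is whether the wider-perspective ICERs can be read as unbiased estimates.

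**Working it through.** The protocol gives no figure for productivity cost, so there is nothing to reproduce. The checks are algebraic, with illustrative inputs marked as assumptions.

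**Notation.** P1 and P0 are the mean productivity losses per person in the intervention and control arms. S = P0 − P1 is the between-arm saving, and SE is its standard error. The protocol's formula is ICER = (C1 − C0)/(E1 − E0).

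**1. Does entering productivity in C1 alone cause bias?** Costing both arms gives the numerator (C1 + P1) − (C0 + P0). Netting the saving in C1 gives (C1 − (P0 − P1)) − C0, which is the same expression. Placement is therefore harmless if the quantity entered is the net difference and it may take either sign.

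**2. What do the possible readings give?** Assumed: C1 = 1,500, C0 = 1,000, QALY gain 0.02, so the base ICER is 500/0.02 = 25,000.

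| P1 / P0 | Both arms costed | Net saving taken off C1 | Only when S > 0 | Intervention arm's own losses taken off C1 |
|---|---|---|---|---|
| 800 / 1,200 | 5,000 | 5,000 | 5,000 | −15,000 |
| 1,000 / 1,000 | 25,000 | 25,000 | 25,000 | −25,000 |
| 1,200 / 800 | 45,000 | 45,000 | 25,000 (base case only) | −35,000 |

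Example, first row: (1,500 + 800 − 1,000 − 1,200)/0.02 = 100/0.02 = 5,000. Taking the arm's own losses off instead: (1,500 − 800 − 1,000)/0.02 = −300/0.02 = −15,000.

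The conditional rule agrees with full costing when work time favours the intervention, but the unfavourable 45,000 is never shown. The last column is the wholly literal reading, in which greater loss of work time makes the intervention look cheaper.

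**3. How large is the selection effect when work time is truly unaffected?** Take S as normal with mean 0, and assume that any S > 0 triggers the analysis.

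- Always included: expected adjustment 0.
- When triggered: E[S | S > 0] = SE × √(2/π) = 0.80 SE.
- Averaged over all trials: 0.5 × 0.80 SE = 0.40 SE.

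In money, assume 10 to 100 working-age participants per arm and an SD of $1,000 to $3,000, with SE = SD × √(2/n). The smallest SE is 1,000 × √(2/100) = $141 and the largest is 3,000 × √(2/10) = $1,342. The spurious saving when triggered is then about $113 to $1,071 per person, and averaged over all trials about $56 to $536 (simulated values, which match theory to within about $1).

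**4. Sensitivity to how the trigger is read.**

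- If a health condition is met independently in half of trials, the trigger rate falls from 0.5 to 0.25; the 0.80 SE when applied is unchanged.
- If the reduction in lost time must be significant at two-sided 5%, it triggers in about 2.5% of null trials. The saving when applied is then about 2.3 SE, and about 0.06 SE averaged over all trials.

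**The case against.** Several objections have force.

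- **C1 alone.** A reader might infer that adjusting only the intervention arm's cost is itself the bias. The documents do not support that. C1 is already defined net of savings, and step 1 shows that netting the between-arm difference there equals costing both arms.
- **Sign.** A reader might infer that the plan really means to subtract the intervention arm's own losses. The surrounding sentences speak of savings both before and after, so losses is most plausibly a slip for savings or losses averted. It still needs correcting, since taken at its word it reverses the sign.
- **One-sided plan.** A reader might infer that the plan as a whole can never show an unfavourable productivity result. That goes too far: the unconditional sensitivity analysis, if followed, would show one. What stands is that the two statements conflict and that the conditional one is biased.
- **Size.** The protocol does not say whether *found to* means a favourable estimate or a significant one, and the health condition lowers the trigger rate further. The 0.80 SE is therefore conditional on an assumption, and no dollar amount follows from the documents.
- **Reach.** The stage is secondary, reported separately and limited to those of working age. This limits the consequence, but separate reporting cannot reveal a result that is never produced.
- **Attendance time.** Secondary outcome measures already lists patients' travel costs, including time, among the intervention resources. Adding all the time spent on sessions could count some of it twice.

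**Conclusion.** The concern holds in limited form. The section contradicts itself on whether the productivity analysis depends on the results, and the conditional version is a one-way rule that biases the recalculated ICERs towards the intervention. With no true work-time effect and a trigger on any favourable estimate, both assumptions, the bias is about 0.80 SE when the rule is applied. A stricter trigger makes it rarer but larger. The description of losses as lowering C1 is a separate sign or wording error. The health-sector base case ICERs and the primary outcome are untouched. The text should be corrected, but this does not threaten the trial's main conclusions.

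**What to change.** Reconcile the two statements in favour of the unconditional one:

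1. Delete the condition that opens "If the intervention is found to successfully improve health outcomes, and to result in reduced time lost from work", and the parenthesis saying that C1 is reduced.
2. Run the productivity sensitivity analysis whatever the results, still reported apart from the base case.
3. Value lost work time in both arms, as C1 + P1 and C0 + P0 or equivalently as a net difference in C1, and let P1 − P0 take either sign. Use losses and savings consistently.
4. Count work time lost to attending sessions only where it is not already in the patient travel and time costs under Secondary outcome measures.

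The cost is mainly wording and slightly more analysis. The HPQ is planned without restriction to one arm, and a reduction in lost time can be judged only by comparing arms, so no new data should be needed; collection in both arms is not stated outright and should be confirmed. The downside for the sponsor is that the wider-perspective ICER may prove less favourable than the base case.
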